## Abstract

**Introduction:**

Coronary artery disease (CAD) persists as a major cause of morbidity and mortality worldwide despite intensive identification and treatment of traditional risk factors. Data emerging over the past decade show a quarter of patients have disease in the absence of any known risk factor, and half have only one risk factor. Improvements in quantification and characterisation of coronary atherosclerosis by CT coronary angiography (CTCA) can provide quantitative measures of subclinical atherosclerosis—enhancing the power of unbiased ‘omics’ studies to unravel the missing biology of personal susceptibility, identify new biomarkers for early diagnosis and to suggest new targeted therapeutics.

**Methods and analysis:**

BioHEART-CT is a longitudinal, prospective cohort study, aiming to recruit 5000 adult patients undergoing clinically indicated CTCA. After informed consent, patient data, blood samples and CTCA imaging data are recorded. Follow-up for all patients is conducted 1 month after recruitment, and then annually for the life of the study. CTCA data provide volumetric quantification of total calcified and non-calcified plaque, which will be assessed using established and novel scoring systems. Comprehensive molecular phenotyping will be performed using state-of-the-art genomics, metabolomics, proteomics and immunophenotyping. Complex network and machine learning approaches will be applied to biological and clinical datasets to identify novel pathophysiological pathways and to prioritise new biomarkers. Discovery analysis will be performed in the first 1000 patients of BioHEART-CT, with validation analysis in the following 4000 patients. Outcome data will be used to build improved risk models for CAD.

**Ethics and dissemination:**

The study protocol has been approved by the human research ethics committee of North Shore Local Health District in Sydney, Australia. All findings will be published in peer-reviewed journals or at scientific conferences.

**Trial registration number:**

ACTRN12618001322224.

Strengths and limitations of this studyBioHEART-CT is a prospective, longitudinal cohort study assessing patients with suspected coronary artery disease (CAD) undergoing CT coronary angiography (CTCA) across multiple Australian centres.Quantitative measures of coronary atherosclerosis from CTCA datasets will be used in conjunction with biological samples, improving the power to discover new mechanisms and markers for CAD.Samples stratified by imaging-quantified disease severity will be analysed by both candidate and unbiased ‘omics’ approaches, using modern technologies and bioinformatic analysis to discover new biomarkers using proteomics, metabolomics, lipidomics, transciptomics, genomics and immunophenotyping.Longitudinal outcome data will be used to build risk models, which can incorporate both traditional and novel risk factors and biomarkers.Limitations of the study include selection bias, as only patients with a clinical indication for CTCA are included, and the geographical isolation of Australia, which may result in the need for confirmation of results in multinational studies.

## Introduction

Cardiovascular disease has persisted as a major cause of human morbidity and mortality despite continual improvements in preventative therapies. In 2015, cardiovascular disease accounted for one-third of all deaths worldwide,^1^ and ischaemic heart disease (IHD) remains the leading cause of years of life lost for high and middle sociodemographic groups internationally.^2^ This large burden of disease puts significant stress on the health systems of individual countries. In Australia, cardiovascular disease remains the number one killer of Australians,^3^ with local health costs estimated to be $A7.7 billion per annum.^4^

The standard modifiable cardiovascular risk factors (SMuRFs)^5^ for atherosclerosis—hypertension, diabetes mellitus, hyperlipidaemia and smoking—were identified in epidemiological studies in the 1960s.^6^ The identification and subsequent efforts to target these risk factors at community and primary care levels have led to a substantial reduction in mortality from cardiovascular disease.^1^ However, substantial disease burden remains and importantly, individual variability in susceptibility to these risk factors is considerable. Conditions, such as impaired glucose tolerance and prehypertension, may also contribute to cardiovascular risk. While continuing our efforts to tackle societal and modifiable risk factors, identifying undiscovered mechanisms that lead to the development of atherosclerosis is critical. Such work will provide new biomarkers for early detection of subclinical atherosclerosis and open avenues for improved preventative and therapeutic strategies that may be relevant to those with and without known risk factors.

The importance of new detection mechanisms for subclinical atherosclerosis is highlighted by interrogating the ‘fine print’ of clinical studies, including information not usually presented in the main tables of manuscripts. Although data regarding the percentage of patients suffering myocardial infarction despite having no SMuRFs are often omitted, a large meta-analysis found that >50% of women and >60% of men presenting with their first acute coronary syndrome (ACS) had 0 or 1 SMuRF,^7^ and similar proportions of SMuRFless patients have been identified in ACS cohort studies.^5 8^ In a recent single centre Australian study, we showed that the proportion of patients presenting with ST-elevation myocardial infarction with 0 SMuRFs has risen from 11% to 27% over an 8-year period.^5^ These patients have developed extensive coronary artery disease (CAD) without having any of the red flags, which would allow doctors to identify their risk of disease and intervene early. Although this is a relatively small piece of the overall IHD pie, the global burden of CAD is immense with an estimated prevalence of 470 million^9^, which makes this 25%–30% SMuRFless patient population important from a public health perspective. It is sobering to think that we have made no clear advances that allow us to identify risk and subclinical disease in this subgroup. Indeed, we also have limited information regarding how these patients respond to traditional secondary preventative strategies, and whether their long-term outcomes and disease progression differs from those with traditional modifiable risk factors.

Further evidence that novel biological mechanisms contribute substantially to atherosclerosis can be seen in results from large scale genome-wide association studies which have reported that 66% of the identified genes conveying heritable cardiovascular risk are not associated with the traditional risk factors.^10^ Many of these genes were related to inflammatory processes, and studies such as the Canakinumab Anti-inflammatory Thrombosis Outcome Study (CANTOS) trial^11^ confirm the importance of inflammation in CAD. However, some of these important genes have not yet been well characterised, and are not yet associated with any known pathway in atherosclerosis and CAD, highlighting the importance of ongoing discovery work.

To address this gap in our understanding of CAD pathophysiology, we have designed a unique cohort study with biobanked samples to facilitate investigation of novel cardiac risk factors and biomarkers. This biobank includes advanced, quantitative imaging measurements of coronary artery atherosclerosis to allow for accurate phenotyping of the patient groups. This overcomes a weaknesses of previous genomics studies that have relied on the presence or absence of a coronary artery event to classify individuals as diseased or as a control, improving the statistical power of the subsequent analysis. The advanced imaging dataset and clinical data, including baseline and follow-up, are integrated with the collection of a broad range of biological samples for discovery work, using state-of-the-art molecular phenotyping platforms and computational bioinformatics.

### Objectives

#### The primary objectives of the BioHEART-CT study are

To identify new biomarkers to assist in early CAD risk identification and stratification.To identify new mechanistic pathways that may be targeted with novel therapeutic strategies to abrogate CAD risk.

#### The secondary objectives of the BioHEART-CT study include the following

To determine the predictive value of a modified CT coronary angiography (CTCA) scoring system for CAD risk which incorporates plaque composition data.To identify new risk factors for CAD based on integration of clinical information profiles, CTCA results and clinical outcomes.To develop a novel risk scoring system incorporating clinical risk factors, novel biomarkers and CTCA scores to more accurately predict CVD events.

## Methods and analysis

### Patient and public involvement

The initial concept for the BioHEART-CT study was prompted by patients who had no known cardiovascular risk factors who presented with ACS and wanted to know ‘why me?’ The ensuing discussions with the patients and their families reinforced the public interest in research in this area. Informal consultation with patient groups through cardiovascular non-profit organisations helped build the initial framework for the study, and patient feedback regarding the recruitment process was sought and was positive in nature. When results of interest to the general public are available, summaries will be posted to the Australia and New Zealand Clinical Trials Registry. Information about this registry is included on the patient information sheet.

### Study type

BioHEART-CT is a multicentre, prospective cohort study of patients with suspected CAD, which brings together detailed clinical information with advanced imaging and molecular phenotyping. Recruitment commenced in 2017 and is ongoing, currently with expansion into a multi-centre study.

#### Study population

A total of 5000 patients will be recruited from participating hospitals and associated imaging sites. All recruitment centres are large tertiary hospitals within the city of Sydney, Australia.

##### Inclusion criteria

Patients who have been referred for CTCA for investigation of suspected CAD.Age 18 years or older.Willing and able to provide informed consent.

##### Exclusion criteria

Patients highly dependent on medical care who are unable to provide informed consent.Patients unwilling or unable to participate in ongoing follow-up.

### Study protocol

#### Screening and enrolment

Eligible patients having a CTCA are invited to participate in the study. Eligibility is confirmed according to the inclusion and exclusion criteria, the study is explained, and informed consent obtained (figure 1).

**Figure 1 F1:**
[figure not shown]
BioHEART-CT study design. CTCA, CT coronary angiography.

#### Patient data collection

The baseline questionnaire is completed by the research staff conducting a face-to-face patient interview. Data obtained include the following information: demographic data including smoking and alcohol intake, medical history, relevant family history, medication history, history of cardiac symptoms and indication for CTCA. Data are entered into secure, encrypted databases in a deidentified format. After recruitment, all patients are assigned a unique study number and all samples, imaging data and demographic information is identified by this number. The master list including identifiable data is securely stored on an encrypted server and is available only to senior research staff. Relevant details are made available to research staff for follow-up purposes.

Participants are contacted by phone at approximately 30 days and then annually to determine if any events have occurred. Information recorded for any potential outcome event includes the acuity, need for hospitalisation and indication for admission, hospital attended, treating physician, date of admission and details of the event. New medical or surgical diagnoses since last contact are also recorded. Participants in BioHEART-CT also consent to review of their electronic medical records and data linkage through the Centre for Health Record Linkage, which will be used for independent medical record reviews.

Significant outcome events that trigger a file review to assess for major adverse cardiovascular events (MACE) or secondary outcomes are the following:

Unstable angina requiring hospitalisation.Heart failure requiring hospitalisation.Acute myocardial infarction.Coronary angiogram with or without percutaneous intervention.Cardiac bypass graft surgery.Aortic or mitral valve surgery.Cerebrovascular accident/transient ischaemic attack.All-cause mortality.

All medical records will be reviewed by an independent adjudication committee to determine if an event should be included in the study results. Detailed criteria for the individual diagnoses included in the outcomes must be met.

MACE is defined as cardiovascular death, non-fatal myocardial infarction or non-fatal stroke. Exploratory outcomes include revascularisation, unstable angina or heart failure requiring hospitalisation.

#### CTCA data acquisition

CTCA scans are obtained on 256 slice scanner, with reconstructions created using appropriate software for the individual machine. Each study is to be protocolled by a radiologist with at least level two accreditation from the Royal Australian and New Zealand College of Radiologists (RANZCR). All radiographers are trained in acquisition and workup of CTCA. Oral metoprolol, or ivabradine if beta blockers are contraindicated, are given to optimise the heart rate if required. Dosing is adjusted by the clinical staff according to baseline heart rate and bodyweight. Oral nitroglycerine (600–800 μg) is given immediately prior to the scan, and iodinated contrast is injected intravenously. Prospective studies are performed if the heart rate is sufficiently controlled, otherwise retrospective acquisition is used. Average dose is minimised at all participating sites in line with current recommendations.^12 13^

#### CTCA imaging analysis

CT data are exported as thin digital imaging and communication in medicine (DICOM) data and are stored securely in a de-identified manner. Data are later analysed using a dedicated workstation to obtain the primary clinical scores at each site. CTCAs are analysed by standard anatomical arterial region as per the 17-segment model outlined by the Society of Cardiovascular Computed Tomography.^14^ Each segment is scored according to degree of stenosis and composition of plaque (calcified, soft and mixed). The segmental scores are aggregated into a modified Gensini score (figure 2), which represents the total amount of calcified and non-calcified plaque present. Calcium scores are generated using the scanner-associated software by the Agatston method. Total raw calcium scores, raw calcium scores for each vessel, and age and sex-matched calcium percentage scores are recorded.

**Figure 2 F2:**
[figure not shown]
Semiquantitative plaque analysis incorporating the established Gensini scoring system^25^ and adding an additional multiplier for plaque composition to create a modified Gensini score. RCA, right coronary artery; PDA, posterior descending artery; PLB, posterolateral branch; LMCA, left main coronary artery; LAD, left anterior descending artery; LCx, left circumflex artery; D1/2, diagonal branch 1/2; OM1/2, obtuse marginal branch 1/2.

Further analysis will be performed at a central core laboratory using a Frontier System (syngo.via, Siemens Healthcare, Erlangen), employing a semiautomated soft plaque algorithm (figure 3).

**Figure 3 F3:**
[figure not shown]
Example of semiautomated analysis of a complex plaque using syngo.via running on a frontier system (Siemens healthcare, Erlangen). (A, B) show a coronary artery lesion with a large calcified component longitudinally and in cross-section. (C, D) show classification of the calcific (yellow) and fibrous (green) components of this lesion.

### Biological sample collection

A 20–30 mL blood sample is taken from an in situ intravenous cannula, or if this is not available, by venesection, prior to CTCA and drug administration. Blood is collected into ethylenediaminetetraacetic acid (EDTA), serum and citrate tubes and stored at 4°C until processing. A lithium heparin tube is collected and processed immediately to extract peripheral blood mononuclear cells (PBMCs) from the buffy coat.

Blood samples are processed by hospital pathology scientists experienced in laboratory procedures. Briefly, whole blood is set aside, then tubes are centrifuged at 1861 x g for 15 min at 4°C prior to aliquoting 500 uL samples of serum, EDTA plasma, whole blood, buffy coat and erythrocytes. The citrate tube is centrifuged at 1861 x g for a second 15 min at 4°C, after which citrate-plasma samples are aliquoted. All aliquoted samples are frozen and stored at −80°C until analysis.

For PBMC isolation, a standard gradient-separation protocol is used.^15^ Briefly, blood from the lithium heparin tube is diluted 1:1 with Hanks’ Balanced Salt Solution (HBSS). Diluted whole blood is then layered on top of Ficoll-Paque Plus and centrifuged (22°C, 1460 x g no brake, 20 min). The buffy coat layer containing PBMCs is then further purified with two wash steps in HBSS using repeat centrifugation as above. PBMCs are then plated at a density of ~2.5×10^4^ cells/cm^2^ into 0.1% gelatin-coated flasks containing endothelial cell growth medium with 2% fetal bovine serum (EGM2 bulletkit, Lonza, Australia) and cultured in standard conditions for up to 21 days with regular monitoring for the spontaneous growth of endothelial progenitor cells (EPCs). Excess PBMCs are immediately frozen in bovine serum (heat-inactivated, Gibco, Australia) containing 10% dimethyl sulfoxide and stored in liquid nitrogen.

### Sample analysis

Samples will be analysed by a variety of methods with the intent of identifying candidate biomarkers and novel metabolites involved in atherosclerosis pathophysiology. There will be two principal approaches used to identify these factors. Table 1 provides a summary of all variables collected and planned assays.

**Table 1 T1:** Summary of variables and planned assays

Clinical variables	Disease quantitation variables	Established markers	Unbiased omics approaches	Candidate approaches
Demographics Standard modifiable cardiovascular risk factors (SMuRFs) Hypertension Hyperlipidaemia Diabetes Smoking Other medical history: BMI Family history of IHD Current medications History of cardiac symptoms	Coronary Artery Calcium Scores Gensini score Modified Gensini score (see figure 2) Frontier System semiautomated plaque analysis (syngo.via, Siemens Healthcare, Erlangen)	Cardiac Troponin NT-proBNP Inflammatory CRP VCAM-1 ICAM-1 IL-6	Metabolomics Proteomics Lipidomics Transcriptomics Genomics Immunophenotyping	Redox signalling dysregulation Endothelial cell signalling dysregulation Soluble factors released by inflammatory plaque Apoptosis signalling Mitochondrial function Angiogenesis potential Disorders of overall coagulation Soluble platelet factors Alpha-gal antibodies Heavy metal toxicities Galectin-3

BMI, body mass index; CRP, C reactive protein; ICAM-1, intercellular adhesion molecule 1; IHD, ischaemic heart disease; IL-6, interleukin-6; NT-proBNP, N-terminal-proB-type natiuretic peptide; VCAM-1, vascular cell adhesion molecule 1.

First is a candidate approach, investigating currently identified factors that are thought to be involved in human biological pathways that could predispose to atherosclerosis. These factors will be assessed within the cohort by specific assays that relate to the biological pathways involved. The candidate areas that have been identified for initial assessment are: soluble factors released by inflammatory signalling within the atherosclerotic plaque, dysregulated redox signalling within the endothelium, disorders of coagulation which lead to hypercoagulable states and/or hypofibrinolysis, soluble platelet factors which indicate platelet dysfunction and dysregulated signalling within endothelial cells as evidenced by assessment of cultured EPCs derived from individual patient samples. Individual assays have been designed to assess each candidate marker or pathway.

The second approach aims to investigate atherosclerosis biology in an unbiased manner by using ‘omics’ techniques. These assessments will use metabolomics, proteomics, transcriptomics, genomics including single nucleotide polymorphism (SNP) arrays and immunophenotyping techniques. The cells used for transcriptomics will be patient-derived EPCs and PBMCs.

Proteomics for the cohort will be assessed using a clinical proteomics platform,^16^ which will give a complete description of the human peptidome in relevant samples, allowing for identification of novel or common factors worthy of further investigation. Metabolomics and lipidomics will be performed using six liquid chromatograpy-mass spectrometry platforms which will allow for identification and quantitation of a broad spectrum of metabolites, including amino acids, nucleotides, neurotransmitters and lipid subtypes.^17–21^

Immunophenotyping will be performed on PBMC samples via mass spectrometry time of flight, which allows for detailed leucocyte phenotyping on an individual basis.^22^ These profiles can be associated with serum levels of established markers of inflammation such as vascular cell adhesion molecule 1 (VCAM-1), intercellular adhesion molecule 1 (ICAM-1) and interleukin-6, as well as correlated with the balance of M1 and M2 phenotype monocytes which have a well-established role in atherosclerosis.^23^

Transcriptomic and genomic assays will be used on subsets of the cohort of particular interest, who for example may display particular resistance or vulnerability to CAD based on traditional risk factor profile and disease burden. Whole transcriptome and RNA sequencing will be performed with ribosomal depletion, and sequencing of the resulting reads and counting will be based on the Genome Encyclopedia of DNA Elements. Whole genome profiling will be performed on individuals with extreme athero-susceptible or athero-resilient phenotype, allowing for unbiased discovery of genetic variants that may be causally associated with the extreme phenotypes.^24^

### Data analysis plan

Statistical machine learning approaches will be applied to these biological and clinical datasets, to identify novel pathophysiological pathways, and to prioritise new markers based on likely causal roles. Discovery analysis will be performed in the first 1000 patients of BioHEART-CT, with validation in the following 4000 patients recruited, and in international collaborators studies (figure 4). Sample size planning for developing classifiers using the high-dimensional data is based on the National Institute of Health (NIH) Biometric online calculator, assuming 1.3-fold standardised change, 50 000 molecular variables and balanced extreme groups.

**Figure 4 F4:**
[figure not shown]
Overview of the analytic approach. CAD, coronary artery disease; RF, risk factor; SMuRF, standard modifiable cardiovascular risk factor.

Biomarker and risk factor data analysis will depend on the specifics of the assay or investigation performed. Generally, continuous variables will be presented as means (with SD) or medians (with IQRs), categorical variables as proportions (%) with X^2^ or Fisher’s exact test used to determine differences between groups. Hazard ratios for a 1 SD increase in a biomarker, after log transformation to remove effects of outliers, on MACE will be obtained from weighted Cox regression models. All p values reported will be two sided, with the 5% threshold used to determine significance.

For testing the prognostic value of prioritised biomarkers, and assuming a C-statistic of 0.75 for traditional risk factors, we estimate that we will require 705 participants to detect a C-statistic of 0.85 with p=0.05, power of 80% and an event rate of 20%. Models developed with different sets of variables and biomarkers and C-statistics for 1-year risk will be determined and compared. The model’s ability to discriminate and reclassify 1-year risk will be assessed using the integrated discrimination index and the net reclassification improvement.

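### The article sets a two-sided 5% threshold for every reported p value and names no multiplicity control, although the same plan is sized for 50 000 molecular variables

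*Protocol article*

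**What the plan says.** All the relevant text is in the protocol article, mostly under Data analysis plan.

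- **Threshold.** After the paragraph on general methods, the article states: "All p values reported will be two sided, with the 5% threshold used to determine significance". The sentence immediately before it plans per-biomarker tests: "Hazard ratios for a 1 SD increase in a biomarker, after log transformation to remove effects of outliers, on MACE", from weighted Cox regression. The rule therefore reaches biomarker tests and is not confined to baseline tables.
- **Scale.** Sample size for the high-dimensional classifiers is planned "assuming 1.3-fold standardised change, 50 000 molecular variables and balanced extreme groups".
- **Method of discovery.** "Statistical machine learning approaches will be applied to these biological and clinical datasets", with markers then ranked by how likely they are to be causal.
- **Two stages.** "Discovery analysis will be performed in the first 1000 patients of BioHEART-CT, with validation in the following 4000 patients recruited". The same sentence goes on to name international collaborators' studies as a further validation source.
- **Flexibility.** "Biomarker and risk factor data analysis will depend on the specifics of the assay or investigation performed".

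No section gives a false discovery rate, a family-wise or genome-wide threshold, or a separate level for discovery or validation.

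**The concern.** The first primary objective is to find new biomarkers, and the second is to find new mechanistic pathways. Both depend on separating true associations from chance ones across several omics platforms. A 5% level suits a single prespecified test. Applied marker by marker at the scale for which the plan is sized, it lets through a large number of null markers, and a second pass at the same 5% removes most of them but not all.

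The consequences extend beyond the first report. Under the secondary objectives, novel biomarkers enter a new risk score. The Discussion intends to take markers and their pathways into cellular and animal models and then towards prospective trials. False markers use resources at each of these steps.

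This is more than silence on a detail left to an analysis plan. The article fixes a level and gives it the widest scope, all reported p values. An analysis plan that set a stricter nominal level for omics tests would depart from the published sentence.

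**Working it through.** **1. The plan's own figure at the 5% level.** The article requires 705 participants to detect a C-statistic of 0.85 against 0.75, with p=0.05, 80% power and a 20% event rate. With the binormal variance V = 0.0099·exp(−a²/2)·[(5a²+8) + (a²+8)/k], a = 1.414·z(AUC) and k = 4 non-events per event:

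- V(0.75) ≈ 0.0928 and V(0.85) ≈ 0.0720.
- Events = [1.960·√(2·0.0928) + 0.842·√(0.0928+0.0720)]² / 0.10² = 140.7, so 141.
- 141/0.20 = 705, an exact match (two-sided, correlation 0).

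The figure is sound for one comparison and contains no allowance for more than one.

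**2. Inputs for the error count.** From the article: m = 50 000 variables, α = 0.05 two-sided, and separate patients for discovery (first 1000) and validation (next 4000). Assumed: every variable is tested with a reported p value, every significant one is retested at 5%, and the share of null variables π₀ is 50% to 100%.

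**3. Expected false positives.**

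- Discovery: m·π₀·α
- Also significant at validation, either direction: m·π₀·α²
- Also significant at validation, same direction: m·π₀·α·(α/2)

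| Null share | Discovery | Validated, either direction | Validated, same direction |
|---|---|---|---|
| 100% | 2500 | 125 | 62.5 |
| 90% | 2250 | 112.5 | 56.3 |
| 50% | 1250 | 62.5 | 31.3 |

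For smaller panels with all variables null, 20 000 variables give 1000, then 50 or 25. With 5000 variables the counts are 250, then 12.5 or 6.3.

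A simulation with 50 000 independent nulls and 200 replicates gave means of 2500 at discovery, 127 validated in either direction (95% range 105 to 148) and 63 in the same direction (47 to 79). Correlation between markers widens the spread but leaves the expected counts unchanged.

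**4. What correction would cost at discovery.** Bonferroni over 50 000 gives 0.05/50 000 = 0.000001 per test. Assume a 0.3 SD difference between two groups of 500. Power then falls from 99.7% at 5% to 44% at that level. This is why false discovery rate control suits discovery better than Bonferroni.

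**5. What correction would cost at validation.** Assume 100 markers carried forward, so α = 0.05/100 = 0.0005 with critical value 3.48.

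- Continuous plaque measure, assumed r = 0.10, n = 4000: z = atanh(0.10)·√3997 = 6.34, and Φ(6.34 − 3.48) ≈ 0.998.
- Cox test on MACE, assumed hazard ratio 1.3 per SD, D events: power ≈ Φ(√D·ln 1.3 − critical value). With 80 events (2% of 4000), Φ(2.35 − 3.48) ≈ 13%. With 200 events (5%), Φ(3.71 − 3.48) ≈ 59%. With 800 events (the article's 20% rate), power is near 100%.
- The same Cox test with 10 markers carried forward (α = 0.005, critical value 2.81): Φ(2.35 − 2.81) ≈ 32% with 80 events and Φ(3.71 − 2.81) ≈ 82% with 200.

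**The case against.** The strongest case against has four parts.

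- **The two numbers belong to different analyses.** The 50 000 is a planning input for classifiers, and a classifier need not report 50 000 p values. The 5% sentence follows descriptive statistics, group comparisons and Cox models in a later paragraph. This stands as a limit on size: nowhere does the article say that each variable is screened at 5%. It does not remove the problem, because the 5% sentence covers all reported p values and directly follows per-biomarker Cox tests.
- **Not every hit is carried forward.** Markers are prioritised on likely causal role, and under Sample analysis the transcriptomic and genomic assays are run only on subsets. The first point makes the step from 2500 to 125 an upper-range case. Running an assay on fewer patients does not by itself lower the expected false positives at discovery, but a variable not measured in both sets cannot be retested.
- **There are further filters.** Validation in collaborators' studies is planned, and preclinical work is meant to test causality. One external retest at 5% would leave 125 × 0.05 = 6.25 markers, or 62.5 × 0.025 = 1.6 with the same direction required. This stands. However, no threshold is stated for the external step, and it does not correct claims made from BioHEART-CT alone.
- **The 5% could refer to adjusted p values.** The sentence does not say nominal or uncorrected, and analysis is allowed to vary by assay. The reading is possible, but nothing in the article supports it, and the one reproducible calculation at p=0.05 is an unadjusted single comparison.

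A reader might infer that thousands of false markers will be declared, that dozens will certainly validate, or that the 4000-patient validation is the only safeguard. The article does not support these readings, for the reasons above.

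**Conclusion.** The point holds in conditional form. The article states a threshold with the widest possible scope and no multiplicity control, in a plan sized for 50 000 variables. Followed as written for marker-level tests, it gives the false-positive counts in the table. Those counts rest on three assumptions: every variable is tested by a reported p value, all significant markers are retested, and the 5% level also governs validation. The last follows from the scope of the sentence and is not stated separately. The real number could be well below the table, depending on how many marker-level p values are reported and how many markers are carried forward. The direction of the problem does not depend on a complete null or on the full 50 000, as the rows for 50% null and the smaller panels show.

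**What to change.** Replace the threshold sentence with a rule by type of test:

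1. **Unadjusted two-sided 5%** only for a short prespecified list of clinical or single-candidate tests.
2. **Discovery, omics marker-level tests:** control the Benjamini-Hochberg false discovery rate at 5% within each platform, with a genome-wide threshold for SNP arrays.
3. **Validation:** test only the markers carried forward, require the same direction as at discovery, and apply Holm or Bonferroni over their number.
4. **MACE tests:** keep the number of markers carried forward small, and fix it with the expected number of events in view.

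The change is to wording; the existing discovery and validation split already supports it, and the classifier work need not alter. If the intention was always that 5% applies to adjusted p values, the sentence should say so and name the adjustment.

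The cost is the loss of some borderline hits. For continuous plaque measures available in all 4000 validation patients the loss of power is slight under the assumptions shown. For Cox tests on MACE it can be material when events are few, and shortening the list recovers only part of it, as the comparison of 100 with 10 markers shows.
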